## Abstract

**Introduction:**

Chronic diseases and falls substantially contribute to morbidity/mortality among seniors, causing this population to frequently seek emergency medical care. Research suggests the paramedic role can be successfully expanded to include community-based health promotion and prevention. This study implements a community paramedicine programme targeting seniors in subsidised housing, a high-risk population and frequent users of emergency medical services (EMS). The aims are to reduce EMS calls, improve health outcomes and healthcare utilisation.

**Methods/analysis:**

This is a pragmatic clustered randomised control trial in four communities across Ontario, Canada. Within each, four to eight seniors’ apartment buildings will be paired and within each pair one building will be randomly assigned to receive the Community Health Assessment Programme through EMS (CHAP-EMS) intervention, while the other building receives no intervention. During the 1-year intervention, paramedics will run weekly sessions in a common area of the building, assessing risk factors for cardiovascular disease, diabetes and falls; providing health education and referrals to community programmes; and communicating results to the participant's primary physician. The primary outcomes are rate of emergency calls per 100 residents, change in blood pressure and change in Canadian Diabetes Risk (CANRISK) score, as collected by the local EMS and study databases. The secondary outcomes are change in health behaviours, measured using a preintervention and postintervention survey and healthcare utilisation, available through administrative databases. Analysis will mainly consist of descriptive statistics and generalised estimating equations, including subgroup cluster analysis.

**Ethics/dissemination:**

This study is approved by the Hamilton Integrated Research Ethics Board and will follow the Tri-Council Policy Statement. Findings will be disseminated through reports to local stakeholders, publication in peer-reviewed journals and conference presentations.

**Trial registration number:**

NCT02152891.

Strengths and limitations of this studyThis study will evaluate a new model of healthcare, better using the skills and training of paramedics to deliver a health assessment, prevention and promotion intervention in their community.A strength of this study is the randomised controlled design and the pragmatic approach to encourage applicability to real world clinical practice and policy.Also, this study applies an adaptation of an intervention already demonstrated to reduce hospitalisations for cardiovascular disease in other settings.Not every community will have subsidised housing buildings for seniors, which will limit the generalisability of our findings. However, this setting is sufficiently common that the results will be valuable to many communities.

## Introduction

Morbidity from chronic diseases and falls causes many older adults to seek emergency medical care. In 2007, chronic diseases (including cardiovascular diseases (CVDs) and diabetes) were responsible for 79% of all deaths in the Canadian province of Ontario.^1^ Similar rates are observed nationally and internationally,^2^ leading the WHO to develop a global strategy to reduce chronic disease by addressing the common risk factors (physical inactivity, unhealthy diet, tobacco use and harmful use of alcohol).^3^ Chronic diseases are strongly correlated with ageing and it is projected that by 2031, nearly 25% of Ontario residents will be 65 years or older.^4^ These diseases diminish quality of life and the potential of our communities,^1^ and, hence, it is important to strive for chronic disease prevention and management among older adults.

Elevated blood pressure (BP) is a readily preventable cause of CVD, and the WHO has identified high BP as a leading risk factor for death.^5^ In addition, hypertension and diabetes frequently coexist, which further compounds the challenges of avoiding CVD. In Canada, 63% of adults with diagnosed hypertension also had diagnosed diabetes.^6^ It is forecast that with the increasing incidence of diabetes, 3.7 million Canadians will be living with this illness by 2018–2019.^7^

In addition to CVD and diabetes, falls contribute to morbidity among older adults. It is estimated that one in three persons over the age of 65 is likely to fall at least once each year,^8^
^9^ and every 30 min an older adult in Ontario is admitted to hospital due to a fall.^10^ Falls decrease quality of life, impact the individual's ability to continue living within the community and are the sixth most common causes of death among seniors.^10^ Most importantly, almost all falls can be avoided through proper screening, intervention and prevention.

Studies have shown that older adults account for more than a third of all Emergency Medical Service (EMS) calls related to cardiopulmonary conditions, diabetes and falls.^11–14^ This may be due to the fact that older adults with high comorbidity (>3 chronic conditions) report poorer health, take more prescription medications and have the highest rate of healthcare visits.^15^ Data from Hamilton Paramedic Service indicate that tenants in ‘seniors’ buildings’ in underserved areas of lower socioeconomic status in Hamilton, a medium sized city in Canada, with a population of just over 500 000 people, are the most frequent callers to the emergency 911 medical service. On average, each paramedic visit and subsequent mandatory hospital emergency department (ED) visit costs around $1044 Canadian dollars.^16^
^17^ Therefore, interventions that reduce the escalation of EMS calls and ED visits could provide potential savings to the healthcare system. Current government approaches being explored include looking for programmes that reallocate existing resources to decrease the use of ED resources.

Studies expanding the role of paramedics to include health promotion and referral to appropriate health service providers have been successfully implemented in other settings. However, this research has been limited to case studies, mostly in rural Australia.^18–20^ Previous studies have shown that paramedics were seen as an underused human resource in rural and remote areas.^18^ Expanded roles included both clinical and primary care, such as community education and engagement, preventive services, treatment of minor illness (and locally endemic conditions) and promotion of lifestyle change to prevent and manage chronic disease.^18^
^20^ A qualitative evaluation showed that these roles were acceptable to the paramedics and were appreciated by the community. Another study, conducted in the UK, evaluated expanding the roles of paramedics in responding to calls from the elderly living in urban areas;^19^ paramedics were given the additional role of referring patients to a general practitioner, district nurse and/or community social services, when needed.

In partnership with Hamilton Paramedic Services and City Housing Hamilton, our team has created a unique multifaceted intervention with health risk assessment (CVD, diabetes and falls), health education/promotion, appropriate referral and feedback to the family physician targeting the issues experienced by seniors that often lead to EMS calls. The intervention is called the Community Health Assessment Programme through E MS (CHAP-EMS) and is based on the Cardiovascular Health Awareness Programme (CHAP) model that focused on hypertension assessment^21^ and the Community Health Awareness of Diabetes (CHAD) Programme, which added screening for diabetes.^22^
^23^ CHAP is a community-based, primary care-centred, volunteer-led, free CVD risk assessment and blood pressure (BP) monitoring programme that was demonstrated in a community cluster randomised control trial to reduce annual hospital admissions at the population level due to stroke, heart failure, and heart attacks by 9% in people aged 65 and over in Canada.^21^ CHAD was a community adaptation of CHAP in which the addition of a diabetes risk assessment tool was demonstrated to be feasible in one community, and had potential to identify individuals with diabetes earlier than through usual care.^23^ The CHAP-EMS programme adapts CHAP and CHAD by extending individual-level and population-level strategies for primary prevention and ‘closes the loop’ by linking participants to follow-up care. Unlike CHAP and CHAD, CHAP-EMS provides its sessions within a common area of the seniors’ apartment buildings, increasing accessibility for a population that may find it difficult to attend programmes in the community. Also, CVD screening in the CHAP-EMS programme includes measurement with a clinically-validated, professional automated BP machine that takes multiple measures and provides an average. Screening also includes diabetes risk assessment using the CANRISK tool,^24^ and screening for fall risk using the Timed Up and Go test.^25^ Finally, CHAP-EMS utilises existing resources such as local wellness programmes, referrals to Community Care Access Centre (CCAC) and staffing by accommodated paramedics (paramedics with personal physical limitations due to injury or pregnancy) trained in health promotion.

The CHAP-EMS pilot was conducted weekly for 1 year in one seniors’ building.^26^ During this period, 79 residents attended the sessions and 48 residents (61%) visited more than once; 40.7% were identified as having undiagnosed elevated BP, and after five visits the mean BP dropped significantly. Similarly, 66.7% of participants had moderate or high risk of developing diabetes, based on their CANRISK score; at their 6-month follow-up, 15% dropped to a lower risk category. Finally, the number of EMS calls decreased by 25% (CI 17.3 to 34.0%) compared to the 12 months preintervention.^26^ Since initial pilot testing was so promising, it is necessary to conduct a robust evaluation of the effectiveness of the CHAP-EMS Programme using randomised controlled trial methodology to understand the effectiveness of CHAP-EMS once scaled up and applied across a number of settings. The evaluation aims to answer the following research questions:

### Primary questions

Will there be a *difference in the rate of EMS calls* in subsidised seniors’ housing buildings receiving the CHAP-EMS programmes compared to buildings not receiving the programme?Will there be a *change in measured systolic and diastolic BP* in senior residents living in subsidised seniors’ housing after receiving the CHAP-EMS programme compared to their own baseline measurement?Will there be a *difference in 10-year diabetes risk, as measured using the CANRISK tool,* in senior residents living in subsidised seniors’ housing after receiving the CHAP-EMS programme (healthy lifestyle education) compared to their own baseline measurement?

### Secondary questions

Will there be a *difference in the health perceptions, behaviours, intentions regarding behaviours, health literacy and knowledge of resources* in senior residents living in subsidised seniors’ housing after receiving the CHAP-EMS programme compared to their own baseline measurement, and compared to seniors in a building not receiving the programme?*Will there be a difference in health-seeking behaviour (eg, number of hospital emergency room visits and primary care visits)* by senior residents living in subsidised seniors’ housing compared to baseline, and compared to seniors in a building not receiving the programme?

## Methods and analysis

### Study design

This study is designed as a pragmatic clustered randomised controlled trial with parallel intervention and control groups. The trial will occur in the Hamilton, York, Guelph, Sudbury and Simcoe regions of Ontario, Canada; a current list of participating regions can be found on clinicaltrials.gov under trial number NCT02152891(see online supplementary appendix A). Within each region, up to eight buildings will be selected and paired based on their characteristics. Within each pair, one building will be randomly allocated to receive the intervention and the other building will act as its control. The programme will be delivered for 1 year in the intervention buildings. Outcomes will be analysed using parallel comparisons (of intervention vs control buildings) as well as preintervention and postintervention comparisons. Process evaluation will be carried out after the 1 year study implementation and will assess the programme implementation in terms of efficiency of the processes in its delivery, participation rates, compliance and ways of improving it. All operations will be overseen by the research team at the Department of Family Medicine, McMaster University, with advice from local stakeholders (eg, public health). Local EMS will monitor the intervention session staffing on a day-to-day basis.

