### Data gathering procedures

Rates of EMS calls, ED visits, primary care visits and other healthcare utilisation will be collected from the administrative database of the local paramedic services, hospital ED databases, Institute for Clinical Evaluative Sciences (ICES) databases, the CHAP-EMS database and consenting participants’ primary care charts. Administrative data will be collected preintervention and postintervention, and retrospectively for the 12 months of intervention.

Health perceptions, behaviours and intentions regarding behaviours, health literacy and knowledge of resources related to chronic disease risk factors will be collected from consenting participants using an interviewer-led survey called the Health Awareness and Behaviour Tool (HABiT). This questionnaire covers the following domains: demographics, health status and quality of life, knowledge and risk factors (cardiovascular and diabetes), health utilisation and access to healthcare, and perceived concern and understanding of risk. It was developed by the research team, loosely based on existing validated questions. It has been pretested, piloted and validated in a sample of older adults in Ontario. Each item will be assigned a score and participant questionnaire results will be summarised as numerical scores. These outcomes will be analysed at the individual level and linked to administrative databases.

There will be two periods of data collection with the HABiT survey: a preintervention survey for residents of the intervention and control buildings administered up to 3 months prior to the intervention, and a postintervention survey administered up to 3 months immediately postintervention. Residents will be notified about the surveys through presentations at tenant engagement meetings, word-of-mouth and posters within the buildings. Surveys will be administered by trained college/university students and research assistants.

Physical measures (eg, BP, weight), risk assessment scores and process outcomes will be collected through the CHAP-EMS electronic database. The database is encrypted, and only accessible to the research team and the paramedics implementing the study.

Any urgent medical concerns identified or similar adverse events will be handled following protocol (eg, phoning the primary physician or EMS, depending on the level of urgency); these events will be recorded and reported to the ethics committee where appropriate.

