### Data analysis

We will use an intention-to-treat analysis and generalised estimating equations (GEE) assuming a Poisson distribution and an exchangeable correlation structure within a building to evaluate healthcare utilisation, BP and risk assessment scores, as well as to identify factors contributing to these outcomes. Rate of EMS calls will be analysed at the building-level only, using GEE. We will perform pairwise comparisons of outcomes for each month during the preintervention and intervention periods. We will identify trends in the outcomes during the preintervention and postintervention observation periods. Subgroup analysis by clusters (each building) and by location will be performed. The HABiT survey data will be summarised as a numerical score representing the participants’ perceptions and behaviours regarding CVD and diabetes, and analysed with GEEs. The intracluster correlation coefficient (ICC) will be computed to determine the effect of clustering (by the building the participants reside in) on the participants’ scores. Other outcomes will be analysed using descriptive statistics.

All analyses requiring health administrative data will be performed in a two-step process. First, CHAP-EMS data with identifiers will be securely transferred to ICES for health record linkage, as per the participant consent form. Once linked, the data set will be de-identified for subsequent analysis. All analyses will be performed using SPSS V.20. Statistical significance will be set at α=0.05 and adjusted using the Bonferroni method for secondary analyses. Results will be reported as rate ratios, 95% CIs and associated p values.

Twice a month, the CHAP-EMS data will be reviewed and analysed to assess for errors in data entry, and assure fidelity to the planned intervention (eg, monitor referral patterns by EMS personnel and proper use of the screening tools). This trial did not warrant formal externally managed data monitoring, or a formal committee, due to its minimal risks. Instead, interim analysis will be conducted on the process measures to evaluate intervention recruitment and implementation, and to provide regular reports to local stakeholders (eg, EMS, public health, local housing). Collaborative research agreements with local partners (eg, housing) specify that aggregate data will be shared with these local stakeholders. Individual data will not be released without written permission from the participant.

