
One limitation of our approach is that not every location will have subsidised housing buildings containing a majority of seniors, which will limit the generalisability of our findings. However, in Canada, this setting is sufficiently common, and that is critical in testing this strategy. Also, the study is focused on more urban areas with a large population of seniors living within a certain locale, and therefore the results will be limited to similar settings.

With our team's experience in implementing and evaluating the CHAP trial, we believe that expanding the programme to serve seniors living in subsidised housing, adding diabetes and falls screening and utilising accommodated paramedic personnel to run the programme, will be effective in lowering rates of EMS calls and ED visits through increasing risk factor detection and awareness, health education and referral to appropriate services. The relative decrease in EMS calls and ED visits will have implications in terms of healthcare savings. At the current time, real findings of this nature are not available and we need more research to understand what is clinically and policy-wise relevant. We also believe that the programme can improve the health behaviour of building occupants, which is expected to improve health outcomes. Such findings will have significant policy implications in favour of its widespread implementation. This study is in keeping with Canada's *Living Longer, Living Well* strategy^32^ for utilising allied health professionals more appropriately and extending their roles within health promotion and disease prevention. It addresses the question of the effectiveness of a novel form of health services delivery on healthcare processes, health outcomes and health resource utilisation.

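### For the secondary outcomes measured in both arms, change from baseline and difference from control stand as equal questions with no rule for which decides, so a change shared by both arms can be read as a programme effect

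*Protocol article*

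**What the plan says.** All references are to the protocol article.

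- **Study design** puts two kinds of comparison side by side without ranking them: "Outcomes will be analysed using parallel comparisons (of intervention vs control buildings) as well as preintervention and postintervention comparisons".
- **Secondary questions** builds both into each question. Health perceptions, behaviours and the related survey outcomes are "compared to their own baseline measurement, and compared to seniors in a building not receiving the programme". Health-seeking behaviour (ED and primary care visits) is "compared to baseline, and compared to seniors in a building not receiving the programme".
- **Data gathering procedures** shows that the survey outcomes have a randomised comparator: "a preintervention survey for residents of the intervention and control buildings administered up to 3 months prior to the intervention", with a second survey after the intervention.
- **Data analysis** names GEE, monthly pairwise comparisons and trends, and the text after it gives the analysis times. Neither says which contrast decides a secondary outcome. On multiplicity: "Statistical significance will be set at α=0.05 and adjusted using the Bonferroni method for secondary analyses".
- **Primary questions** is narrower. EMS calls are asked about only between buildings: "receiving the CHAP-EMS programmes compared to buildings not receiving the programme". BP and CANRISK are asked about only "after receiving the CHAP-EMS programme compared to their own baseline measurement".

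**The concern.** The two contrasts test different things. Intervention versus control buildings isolates what randomisation assigned. Before versus after within intervention buildings also picks up season, secular trend, a year of ageing and a second pass through the same questionnaire.

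If both arms move together and the programme does nothing, the first null hypothesis is true and the second is false. The same data can then show an improvement on baseline and no difference from control. As the questions are worded, the first result answers half of what was asked, and nothing in the plan says that it yields to the second.

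This matters because the Discussion expects fewer ED visits and better health behaviour, and says of the results: "Such findings will have significant policy implications in favour of its widespread implementation". A policy claim could rest on the uncontrolled contrast although a randomised one is available.

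**Working it through.** The protocol gives no figure for these secondary contrasts, so there is none to reproduce. The check asks how often a shared change would be declared significant under the plan's Bonferroni rule when the programme has no effect.

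**Inputs**

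- From the protocol: α = 0.05, with Bonferroni for secondary analyses. I take the tests as two-sided.
- Assumed: 300 HABiT respondents in the intervention arm, surveyed before and after; pre-post correlation 0.5; no clustering; 7 secondary outcomes, so 7 tests with one contrast each or 14 with two; shared shifts of 0.05, 0.1 and 0.2 SD.

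**Step 1: before-after test, HABiT**

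Standard error of the mean change, in SD units:

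- paired: √(2(1 − 0.5)/300) = 0.0577
- unpaired: √(2/300) = 0.0816

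The critical value is 1.960 at 0.05 and 2.914 at 0.05/14 = 0.00357. The chance of significance is Φ(shift/SE − critical value), plus a negligible opposite tail.

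| Shared shift | shift/SE, paired | at 0.05 | at 0.05/14 |
|---|---|---|---|
| 0.05 SD | 0.866 | 14% | 2% |
| 0.1 SD | 1.732 | 41% | 12% |
| 0.2 SD | 3.464 | 93% | 71% |

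If responses cannot be paired, a 0.2 SD shift gives 0.2/0.0816 = 2.449, which is significant in 69% of trials at 0.05 and 32% at 0.05/14. For comparison, a valid test with no effect would be positive in 0.36% of trials at 0.05/14. The between-arm test keeps to its nominal level whatever the shared shift, because the shift cancels.

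**Step 2: before-after test, a count outcome**

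The documents give no rate for ED or primary care visits. As a stand-in I used the EMS rate of 44.06 per 100, with 12 pairs of buildings and 58 residents per building (700/12 ≈ 58). I assumed a pair SD of 0.2 and a building-by-year SD of 0.1 on the log scale, and paired t tests on log counts. In 40,000 simulated trials with no programme effect, at 0.05/14:

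| Common fall | before-after significant | between-arm significant |
|---|---|---|
| 10% | about 2% | about 0.3% |
| 15% | about 6% | about 0.3% |
| 20% | about 15% | about 0.4% |

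**Step 3: cost to the randomised contrast**

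Suppose a between-arm test has 80% power at 0.05/7, where the critical value is 2.690. Its standardised effect is then 2.690 + 0.842 = 3.532. If the before-after tests join the family, the critical value rises to 2.914 and power falls to Φ(3.532 − 2.914) = Φ(0.618) ≈ 73%.

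**The case against.** **EMS calls are not open.** A reader might infer from the Study design sentence that the lead outcome also has two equal contrasts. The documents do not support that. The Primary questions ask only about the difference between buildings, Sample size is built on a difference between intervention and control groups, and Control of bias uses the parallel design against seasonality. The Study design sentence also has to cover BP and CANRISK, which are compared only with own baseline. This objection stands and limits the point to the secondary outcomes.

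**Bonferroni applies.** A reader might say that two contrasts at 0.05 nearly double the false-positive rate, to between 8.3% (correlation 0.71) and 9.7% (independent tests). That ignores the adjustment that the plan prescribes for secondary analyses. Bonferroni over the two contrasts alone brings the range back to 4.3% to 4.9%. The objection stands as regards chance findings. It does not answer the bias, because under shared drift the before-after null hypothesis is false.

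**The drift is assumed.** No document gives a shared shift, and at 0.05 SD the risk is small. Hence the range above.

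**The questions say that both contrasts are asked.** If both had to be positive, the simulation in Step 2 gives under 3% false positives even at 0.05, for falls up to 20%. But the text states neither an either-one nor a both rule, and that gap is the point.

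**Regression to the mean** might be added to the list of biases. The protocol selects neither buildings nor survey respondents on extreme values, so I leave it out.

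**The SAP may settle it.** Ranking secondary contrasts is often left there. But the protocol itself makes the before-after contrast a question in its own right, and a SAP that follows it would carry the ambiguity on.

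**Conclusion.** The point holds for HABiT outcomes and for ED and primary care visits. The protocol makes an uncontrolled contrast a question of equal rank with the randomised one and does not subordinate it.

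How much this matters depends on drift that the documents do not give. Under the stated assumptions and Bonferroni over 14 tests, it is minor for a shared HABiT shift of 0.05 SD (2%), material at 0.1 SD (12%) and serious at 0.2 SD (71% paired, 32% unpaired). Leaving out clustering in the HABiT figures makes them illustrative. The fall in power from 80% to about 73% depends on the assumed 7 and 14 tests.

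For EMS calls, all that remains is that Data analysis does not repeat the contrast already chosen. The change is worth making because it costs little and protects the comparison that randomisation supports.

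**What to change.** 1. In Secondary questions and Data analysis, state that for HABiT scores and health-care use the deciding contrast is intervention versus control buildings, adjusted for baseline. Reword the questions so that comparison with baseline is no longer a test of its own.
2. Choose the form of adjustment to suit the data. Control of bias calls the surveys anonymous, while Data gathering procedures says individual results are linked to administrative databases. If a person's two surveys can be linked, use the individual baseline value. Otherwise use the building's baseline mean or an arm-by-period term.
3. Report before-after changes descriptively for both arms, so that shared drift is visible, and keep them outside the Bonferroni family.
4. For EMS calls, carry the between-building contrast from Primary questions and Sample size into the analysis text.

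The cost is wording, with no new data. The downside is that an improvement within intervention buildings can no longer be claimed as a significant result on its own.
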